## Appendix 5. Creatinine Clearance Formula

---

**Note:** This formula is to be used for calculating creatinine clearance (CrCl) from **local laboratory results only**.

*For serum creatinine concentration in mg/dL:*

$$\text{CrCl} = \frac{(140 - \text{age}^a) \times (\text{wt}) \times 0.85 \text{ (if female), or } \times 1.0 \text{ (if male)}}{72 \times \text{serum creatinine (mg/dL)}} \text{ (mL/min)}$$

*For serum creatinine concentration in  $\mu\text{mol/L}$ :*

$$\text{CrCl} = \frac{(140 - \text{age}^a) \times (\text{wt}) \times 0.85 \text{ (if female), or } \times 1.0 \text{ (if male)}}{0.81 \times \text{serum creatinine } (\mu\text{mol/L})} \text{ (mL/min)}$$

---

a Age in years, weight (wt) in kilograms.

Source: Cockcroft and Gault 1976.

---

## Appendix 6. Protocol JPCE Inducers and Strong Inhibitors of CYP3A

---

The information in this table is provided for guidance to investigators and does not preclude the use of these medications if clinically indicated.

---

### Strong Inducers of CYP3A

Carbamazepine  
Dexamethasonea  
Phenobarbital/phenobarbitone  
Phenytoin  
Rifapentine  
Rifampin  
Rifabutin  
St John's wort

---

### Moderate Inducers of CYP3A

Bosentan  
Lesinurad  
Modafinil  
Primidone  
Telotristat ethyl

---

### Strong Inhibitors of CYP3A

Aprepitant  
Ciprofloxacin  
Clarithromycin  
Conivaptan  
Diltiazem  
Erythromycin  
Fluconazole  
Itraconazole  
Ketoconazole  
Nefazodone  
Posaconazole  
Troleandomycin  
Verapamil

---

a Important note: All patients may receive supportive therapy with dexamethasone, preferably for  $\leq 7$  days, if clinically indicated.

---

## Appendix 7. RECIST 1.1 and irRECIST Criteria

---

Response and progression will be evaluated in this study using the international criteria proposed by the New Response Evaluation Criteria in Solid Tumors (RECIST): Revised RECIST Guideline (version 1.1; Eisenhauer et al. 2009) (as a secondary objective) and by the immune-related Response Evaluation Criteria in Solid Tumors (irRECIST) (as an exploratory objective only).

### RECIST 1.1

#### Measurability of Tumor at Baseline

Tumor lesions/lymph nodes will be categorized at baseline as measurable or nonmeasurable. Measurable disease is defined by the presence of at least 1 measurable lesion.

##### *Measurable*

Tumor lesions: Measured in at least 1 dimension (longest diameter in the plane of measurement is to be recorded) with a minimum size of:

- 10 mm by computed tomography (CT) or magnetic resonance imaging (MRI) scan (slice thickness  $\leq 5$  mm)
- 10 mm caliper measurement by clinical exam (nonmeasurable lesions if cannot be accurately measured with calipers)
- 20 mm by chest X-ray.

Malignant lymph nodes: To be considered pathologically enlarged and measurable, a lymph node must be  $\geq 15$  mm in short axis when assessed by CT scan (CT scan thickness recommended to be  $\leq 5$  mm).

##### *Nonmeasurable*

All other lesions, including small lesions (longest diameter  $< 10$  mm or pathological lymph nodes with  $\geq 10$  to  $< 15$  mm short axis) as well as truly nonmeasurable lesions. Lesions considered truly nonmeasurable include: leptomeningeal disease, ascites, pleural/pericardial effusions, lymphangitis cutis/pulmonis, inflammatory breast disease, lymphangitis involvement of skin or lung, abdominal masses/abdominal organomegaly identified by physical exam that is not measurable by reproducible imaging techniques.

#### *Special Considerations for Lesion Measurability*

##### Bone Lesions:

- Bone scan, positron emission tomography (PET) scan or plain films are not considered adequate imaging techniques to measure bone lesions.

- Lytic bone lesions or mixed lytic-blastic lesions, with identifiable soft tissue components, that can be evaluated by cross sectional imaging techniques such as CT or MRI, can be considered measurable lesions if the soft tissue component meets the definition of measurability.
- Blastic bone lesions are nonmeasurable.

#### Cystic Lesions:

- Simple cysts should not be considered as malignant lesions (neither measurable nor nonmeasurable)
- Cystic lesions thought to represent cystic metastases can be considered as measurable lesions, if they meet the definition of measurability. If noncystic lesions are presented in the same patients, these are preferred for selection as target lesions.

#### Lesions with Prior Local Treatment:

- Tumor lesions situated at a previously irradiated area, or in an area subjected to other loco-regional therapy, are nonmeasurable unless there has been demonstrated progression in the lesion.

### **Baseline Documentation of Target and Nontarget Lesion**

#### ***Target Lesions***

When more than 1 measurable lesion is present at baseline, all lesions up to a maximum of 5 lesions total (and a maximum of 2 lesions per organ) representative of all involved organs should be identified as target lesions and will be recorded and measured at baseline. Non-nodal Target lesions should be selected on the basis of their size (lesions with the longest diameter), be representative of all involved organs, and can be reproduced in repeated measurements. Measurable lymph nodes are target lesions if they meet the criteria of a short axis of  $\geq 15$  mm by CT scan. All measurements are to be recorded in the eCRF in millimeters (or decimal fractions of centimeters [cm]).

#### ***Nontarget Lesions***

All other lesions (or sites of disease) are identified as nontarget lesions (chosen based on their representativeness of involved organs and the ability to be reproduced in repeated measurements) and should be recorded at baseline. Measurement of these lesions are not required but should be followed as 'present,' 'absent,' or in rare cases 'unequivocal progression.' In addition, it is possible to record multiple nontarget lesions involving the same organ as a single item on the eCRF (for example, multiple liver metastases recorded as 1 liver lesion).

Lymph nodes with short axis  $\geq 10$  mm but  $< 15$  mm should be considered nontarget lesions. Nodes that have a short axis  $< 10$  mm are considered nonpathological and are not recorded or followed.

### Specifications by Methods of Measurement

All measurements should be recorded in metric notation, using a ruler or calipers if clinically assessed. All baseline evaluations should be performed as closely as possible to the beginning of treatment and never more than 4 weeks before the beginning of the treatment.

The same method of assessment and the same technique should be used to characterize each identified and reported lesion at baseline and during follow up. Imaging-based evaluation is should always be done rather than clinical examination unless the lesion(s) being followed cannot be imaged but are assessed by clinical exam.

An adequate volume of a suitable contrast agent should be given so that the metastases are demonstrated to best effect and a consistent method is used on subsequent examinations for any given patient. If prior to enrollment it is known a patient is not able to undergo CT scans with intravenous contrast due to allergy or renal insufficiency, the decision as to whether a noncontrast CT or MRI (with or without intravenous contrast) should be used to evaluate the patient at baseline and follow up should be guided by the tumor type under investigation and the anatomic location of the disease.

*Clinical Lesions:* Clinical lesions will only be considered measurable when they are superficial and  $\geq 10$  mm diameter as assessed using calipers (for example, skin nodules). For the case of skin lesions, documentation by color photography, including a ruler to estimate the size of the lesion is recommended. When lesions can be evaluated by both clinical exam and imaging, imaging evaluation should be undertaken since it is more objective and may be reviewed at the end of the study.

*Chest X-ray:* Chest CT is preferred over chest X-ray when progression is an important endpoint. Lesions on chest X-ray may be considered measurable if they are clearly defined and surrounded by aerated lung.

*CT and MRI:* CT scan is the best currently available and reproducible method to measure lesions selected for response assessment. Measurability of lesions on CT scan is based on the assumption that CT slice thickness is  $\leq 5$  mm. When CT scan have slice thickness  $> 5$  mm, the minimum size for a measurable lesion should be twice the slice thickness. MRI is also acceptable in certain situations (for example, for body scans). If there is concern about radiation exposure at CT, MRI may be used instead of CT in selected instances.

*Ultrasound:* Ultrasound should not be used to measure lesion size. Ultrasound examinations cannot be reproduced in their entirety for independent review at a later date and, because they are operator dependent, it cannot be guaranteed that the same technique and measurements will be taken from one assessment to the next. If new lesions are identified by ultrasound in the course of the study, confirmation by CT or MRI is advised.

*Endoscopy, Laparoscopy:* The utilization of these techniques for objective tumor evaluation is not advised. However, such techniques can be useful to confirm complete pathological response when biopsies are obtained or to determine relapse in trials where recurrence following complete response (CR) or surgical resection is an endpoint.

*Tumor Markers:* Tumor markers alone cannot be used to assess tumor response. If markers are initially above the upper normal limit, they must normalize for a patient to be considered in CR. Specific guidelines for both prostate-specific antigen (PSA) response (in recurrent prostate cancer) and CA-125 response (in recurrent ovarian cancer) have been published.

*Cytology, Histology:* These techniques can be used to differentiate between partial responses (PR) and CR in rare cases if required by protocol (for example, residual lesions in tumor types such as germ cell tumors, where known residual benign tumors can remain). When effusions are known to be a potential adverse effect of treatment (for example, with certain taxane compounds or angiogenesis inhibitors), the cytological confirmation of the neoplastic origin of any effusion that appears or worsens during treatment can be considered if the measurable tumor has met criteria for response or stable disease (SD) in order to differentiate between response (or SD) and progressive disease.

*Pet Scan (FDG-PET, PET CT):* PET is not recommended for lesion assessment. If a new lesion is found by PET, another assessment must be done by CT, unless the PET CT is of diagnostic quality. If CT is done to confirm the results of the earlier PET scan, the date of progression must be reported as the earlier date of the PET scan.

*Bone Scan:* If lesions measured by bone scan are reported at baseline, it is necessary to repeat the bone scan when trying to identify a CR or PR in target disease or when progression in bone is suspected.

## **Response Criteria**

### ***Evaluation of Target Lesions***

*Complete Response (CR):* Disappearance of all target lesions. Any pathological lymph nodes (whether target or nontarget) must have reduction in short axis to <10 mm. Tumor marker results must have normalized.

*Partial Response (PR):* At least a 30% decrease in the sum of diameter of target lesions, taking as reference the baseline sum diameters.

*Progressive Disease:* At least a 20% increase in the sum of the diameters of target lesions, taking as reference the smallest sum on study (including the baseline sum if that is the smallest). In addition to the relative increase of 20%, the sum must also demonstrate an absolute increase of at least 5 mm. The appearance of one or more new lesions is also considered progression.

For equivocal findings of progression (for example, very small and uncertain new lesions; cystic changes or necrosis in existing lesions), treatment may continue until the next scheduled assessment. If at the next scheduled assessment, progression is confirmed, the date of progression should be the earlier date when progression was suspected.

*Stable Disease (SD):* Neither sufficient shrinkage to qualify for PR nor sufficient increase to qualify for progressive disease, taking as reference the smallest sum diameters while on study.

*Not Evaluable:* When an incomplete radiologic assessment of target lesions is performed or there is a change in the method of measurement from baseline that impacts the ability to make a reliable evaluation of response.

### ***Evaluation of Nontarget Lesions***

*Complete Response:* Disappearance of all nontarget lesions and normalization of tumor marker level. All lymph nodes must be nonpathological or normal in size (<10 mm short axis).

*Non-CR/ non-progressive disease:* Persistence of 1 or more nontarget lesions and/or maintenance of tumor marker level above the normal limits.

*Progressive Disease:* Unequivocal progression of existing nontarget lesions. The appearance of 1 or more new lesions is also considered progression.

*Not Evaluable:* When a change in method of measurement from baseline occurs and impacts the ability to make a reliable evaluation of response.

### **Evaluation of Best Overall Response**

The best overall response is the best response recorded from the start of the study treatment until the earliest of objective progression or start of new anticancer therapy, taking into account any requirement for confirmation. The patient's best overall response assignment will depend on the findings of both target and nontarget disease and will also take into consideration the appearance of new lesions. The best overall response will be calculated via an algorithm using the assessment responses provided by the investigator over the course of the trial.

### ***Time Point Response***

It is assumed that at each protocol-specified time point, a response assessment occurs. (When no imaging/measurement is done at all at a particular time point, the patient is not evaluable (NE) at that time point.) Table 1 provides a summary of the overall response status calculation at each time point for patients who have *measurable disease* at baseline.

**Table 1. Time Point Response: Patients with Target (± Nontarget) Disease**

| Target Lesions      | Nontarget Lesions                            | New Lesions | Overall Response    |
|---------------------|----------------------------------------------|-------------|---------------------|
| CR                  | CR                                           | No          | CR                  |
| CR                  | Non-CR/non-progressive disease               | No          | PR                  |
| CR                  | Not evaluated                                | No          | PR                  |
| PR                  | Non-progressive disease or not all evaluated | No          | PR                  |
| SD                  | Non-progressive disease or not all evaluated | No          | SD                  |
| Not all evaluated   | Non-progressive disease                      | No          | NE                  |
| Progressive disease | Any                                          | Yes or No   | Progressive disease |
| Any                 | Progressive disease                          | Yes or No   | Progressive disease |
| Any                 | Any                                          | Yes         | Progressive disease |

Abbreviations: CR = complete response; PR = partial response; SD = stable disease; NE = inevaluable.

Table 2 is to be used when patients have *nonmeasurable* disease only.

**Table 2. Time Point Response: Patients with Nontarget Disease Only**

| Nontarget Lesions               | New Lesions | Overall Response                            |
|---------------------------------|-------------|---------------------------------------------|
| CR                              | No          | CR                                          |
| Non-CR/non-progressive disease  | No          | Non-CR/non-progressive disease a |
| Not all evaluated               | No          | NE                                          |
| Unequivocal progressive disease | Yes or No   | Progressive disease                         |
| Any                             | Yes         | Progressive disease                         |

Abbreviations: CR = complete response; NE = inevaluable.

a non-CR/non-progressive disease is preferred over SD for nontarget disease.

### Frequency of Tumor Re-Evaluation

A baseline tumor evaluation must be performed within 4 weeks before patient begins study treatment. Frequency of tumor re-evaluation while on and adapted to treatment should be protocol-specific and adapted to the type and schedule of treatment. In the context of Phase 2 studies where the beneficial effect therapy is not known, follow up every 6-8 weeks is reasonable. Normally, all target and nontarget sites are evaluated at each assessment using the same method. However, bone scans may need to be repeated only when CR is identified in target disease or when progression in bone is suspected.

### Confirmatory Measurement/Duration of Response

#### *Confirmation:*

The main goal of confirmation of objective response in clinical trials is to avoid overestimating the response rate observed. The confirmation of response is particularly important in *nonrandomized trials* where response (CR/PR) is the primary end point. In this setting, to be assigned a status of PR/CR, changes in tumor measurements must be confirmed by repeat assessments that should be performed no less than 4 weeks after the criteria for response are first met. To confirm a response of CR, a full assessment of all target and nontarget lesions that were present at baseline must occur, including those measured by bone scan. To confirm a PR or SD, a full assessment of target lesions that were present at baseline must occur; assessment of nontargets is not required.

However, in *randomized trial* (Phase 2 or 3) or studies where SD or progression is the primary endpoint, confirmation of response is not required. But elimination of the requirement may increase the importance of central review to protect against bias, in particular of studies which are not blinded.

In the case of SD, follow-up measurements must have met the SD criteria at least once after start of treatment at a minimum interval not less than 6 weeks measured from first dose.

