| Prior and current medication                       | X                              |   | X                                        |   |                                                                                                                                                                                                                                                                                             |
| AE collection                                      | X                              |   | X                                        |   | CTCAE Version 4.0.                                                                                                                                                                                                                                                                          |
| ECOG performance status                            | X                              |   | X                                        |   |                                                                                                                                                                                                                                                                                             |
| Radiological tumor assessment
(example: MRI/CT) |                                |   | X                                        |   | RECIST 1.1/irRECIST; Scans will be performed and reviewed locally; Done every 6 weeks $\pm$ 7 days from Cycle 1, Day 1 for 48 weeks, then every 9 weeks thereafter. The same method of assessment and technique used at baseline should be used for each consecutive assessment thereafter. |
| Tumor measurement (palpable or visible)            |                                |   | X                                        |   |                                                                                                                                                                                                                                                                                             |

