| Secondary                                                                                                                                                                                                      |                                                                                                                                                                                                                                                                                |
| To assess the preliminary efficacy of abemaciclib in combination with pembrolizumab                                                                                                                                   | 
 
• ORR per tumor assessment using RECIST v1.1
 
• PFS per RECIST v1.1
 
• DoR per RECIST v1.1
 
• DCR per RECIST v1.1
 
• OS
 
                                                                      |
| To characterize the PK of abemaciclib and pembrolizumab when given in combination                                                                                                                                     | Abemaciclib and pembrolizumab concentrations in plasma or serum                                                                                                                                                                                                                |
| Exploratory                                                                                                                                                                                                    |                                                                                                                                                                                                                                                                                |
| To assess the preliminary efficacy (per irRECIST) of abemaciclib in combination with pembrolizumab                                                                                                                    | ORR, PFS, DoR, DCR per tumor assessment using irRECIST                                                                                                                                                                                                                         |

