### 9.1. Efficacy Assessments

Tumor response will be assessed every 6 weeks ( $\pm 7$  days) by investigator, with confirmatory assessment (including disease progression) obtained at the next routine scheduled imaging time point (that is, after 6 weeks  $\pm 7$  days). For the tumor expansion phase, after 48 weeks, tumor assessments will be conducted every 9 weeks. The same method of assessment and technique used at baseline should be used for each consecutive assessment thereafter.

See Section 10.3.2 for definitions of the efficacy endpoints.

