## 10. Statistical Considerations

### 10.1. Sample Size Determination

The primary objective of this study is to further evaluate safety and tolerability of abemaciclib in combination with pembrolizumab after the Phase 1a Study JPBJ. The sample size of Study JPCE was selected to allow adequate assessment of safety at the recommended doses for each tumor type.

Approximately 75 treated patients (approximately 25 per cohort for *KRAS* *mt*, PD-L1+ NSCLC, NSCLC with squamous histology, and HR+, HER2- metastatic breast cancer). A sample size of n=25 and n=75 (combining the 3 cohorts) will provide an 80% confidence interval (CI) of (0, 8.8%) or (0, 3.0%) for the rate of occurrence of an unobserved AE. In addition, for tumor response, under each cohort, with a total sample size of n=25, the 80% CI of the observed response rate is approximately equal to the observed incidence rate +/- 10% to 15%. Example point estimates of incidence rates and corresponding 2-sided 80% CIs are summarized in [Table JPCE.10.1](#). The values are provided as a reference for estimation rather than a basis of any decision criteria.

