**Table JPCE.10.1. Estimated Incidence Rate and Its 2-Sided 80% CI**

| Num. of Cases
(N=25) | Estimate Rate | 80% CI*     |             |
|-------------------------|---------------|-------------|-------------|
|                         |               | Lower Limit | Upper Limit |
| 0                       | 0.0           | 0.0         | 0.09        |
| 3                       | 0.12          | 0.04        | 0.25        |
| 5                       | 0.20          | 0.10        | 0.34        |
| 8                       | 0.32          | 0.20        | 0.47        |
| 11                      | 0.44          | 0.30        | 0.59        |
| 14                      | 0.56          | 0.41        | 0.70        |
| 17                      | 0.68          | 0.53        | 0.80        |
| 20                      | 0.80          | 0.66        | 0.90        |

Abbreviation: CI = confidence interval.

\* 80% Clopper-Pearson interval for binomial distribution with sample size of 25

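### An on-schedule first scan at 35 to 41 days cannot establish stable disease under Appendix 7, so part of DCR depends on the scan date

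*Protocol*

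**What the plan says.** Appendix 7 (RECIST 1.1, under Confirmation) says when stable disease counts: the SD criteria must have been met at least once after treatment starts, "at a minimum interval not less than 6 weeks measured from first dose". No tolerance is given.

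The on-treatment schedule (Table JPCE.2.2) says of tumor scans: "Done every 6 weeks $\pm$ 7 days from Cycle 1, Day 1 for 48 weeks". Section 9.1 repeats the interval and the 7-day window.

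Table JPCE.4.1 lists "DCR per RECIST v1.1" as a secondary endpoint and DCR per irRECIST as an exploratory one. Appendix 7 describes irRECIST as an adaptation of RECIST 1.1.

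On assignment of best response, Appendix 7 says: "The best overall response will be calculated via an algorithm using the assessment responses provided by the investigator". It does so "taking into account any requirement for confirmation", and the SD minimum stands under the Confirmation heading.

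Section 9.1 refers to Section 10.3.2 for the endpoint definitions, but Section 10.3.2 only names DCR. The one place that mentions adjusting for the scan window is footnote c of Table JPCE.10.2. It leaves to the SAP the meaning of two scan intervals in the PFS censoring rules and does not mention SD or DCR.

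**The concern.** The SD minimum and the scan schedule run on the same clock, from first dose. The minimum is set at the centre of the scan window rather than at its lower edge. A site can therefore follow the schedule exactly and still produce a first assessment that cannot count towards SD.

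Two patients with the same disease course, SD at the first scan and progression at the second, would receive different best responses if one was scanned at 41 days and the other at 42. Neither scan is a protocol deviation. Part of a secondary endpoint would then reflect appointment dates rather than disease.

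**Working it through.** The protocol gives no figure for DCR or for this effect, so there is none to reproduce. The check is date arithmetic followed by an illustration of size.

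**1. Permitted first-scan days.** From Table JPCE.2.2: 42 − 7 = 35 to 42 + 7 = 49 days after Cycle 1 Day 1, which is 49 − 35 + 1 = 15 days.

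**2. Days that meet the SD minimum** (6 weeks = 42 days elapsed, Appendix 7).
- Too early: 35 to 41, 7 of 15 days.
- Sufficient: 42 to 49, 8 of 15 days.

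**3. Whether early scans are realistic.** Table JPCE.2.2 allows Day 1 visits up to 3 days early. With 21-day cycles and no delay, Cycle 3 Day 1 falls 42 days after first dose. A scan done 1 to 3 days before that falls at 39 to 41 days: in window, but short of the minimum.

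**4. Who is affected.** The second scan is due at 84 ± 7 = 77 to 91 days. Anyone still SD there qualifies whatever the date of the first scan. The group is limited to patients with SD at an early first scan and no later SD, PR or CR, because of progression, death, new therapy or no further scan.

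**5. Effect per patient.** Section 10.1 plans "approximately 25 per cohort", so one patient is 1/25 = 4 points. As an example with assumed counts, take 8 other disease-controlled patients and k patients with SD at the first scan only:

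| k | DCR if all k scanned at ≥42 days | DCR if all k scanned before 42 days |
|---|---|---|
| 1 | 9/25 = 36% | 8/25 = 32% |
| 3 | 11/25 = 44% | 8/25 = 32% |
| 5 | 13/25 = 52% | 8/25 = 32% |

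**6. Expected size under assumptions.** Loss in DCR = s × p × e, taking scan date as unrelated to outcome.
- s, the proportion with SD at the first scan: assumed 0.40.
- p, the proportion of these progressing at the second scan: assumed 0.30 to 0.50.
- e, the proportion of first scans before 42 days. Uniform over the window: 7/15 = 0.467. Normal around 42 days with standard deviation 3 days, in whole days: Φ((41.5 − 42)/3) = 0.434.

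Results:
- Low: 0.40 × 0.30 × 0.434 = 0.052, and 0.052 × 25 = 1.3 patients.
- High: 0.40 × 0.50 × 0.467 = 0.093, and 0.093 × 25 = 2.3 patients.

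If every first scan fell at 42 days or later (e = 0), the loss would be zero. Deaths, new therapy or missed scans after the first would add to the loss.

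**7. After the change.** With a minimum of 35 days, 0 of the 15 permitted days fall short, against 7 of 15 now.

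**The case against.** The strongest reply is that this detail belongs in the SAP. The protocol does not set out its best-response algorithm, and footnote c of Table JPCE.10.2 shows that the sponsor handles window tolerances there. The SAP is not at hand and may contain one. That stands as a possibility. But the protocol has not left the point open: it states a mandatory minimum, and the footnote covers only PFS censoring. A tolerance in the SAP would depart from the protocol's own text.

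A second reply is that a minimum SD duration and a visit window serve different purposes, and that 35 days is merely a more lenient choice. It is true that 6 weeks is not wrong in itself. The fault is the pairing, under which patients assessed on schedule are classified by scan date.

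A reader might infer more than the documents support:
- **That DCR is biased downward.** DCR has no true value apart from its definition. The shift is downward only relative to a rule that accepts every in-window scan.
- **That sites scanning early will look worse.** The protocol summarizes efficacy by cohort (Sections 10.3.1 and 10.3.2) and plans no comparison between sites.
- **That the historical-control screen is affected.** Section 5.4 names response rate for that purpose, not DCR.

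It also stands that the effect is small beside sampling error. Using the method of Table JPCE.10.1 ("80% Clopper-Pearson interval for binomial distribution with sample size of 25"), 8/25 gives 0.20 to 0.47, as the table shows, and 13/25 gives 0.38 to 0.66, or roughly 14 points either side. That limits the importance of the point, but an arbitrary classification rule is not sampling error and is easily removed.

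**Conclusion.** The concern holds in limited form. The protocol's scan window permits a first scan that its own SD rule cannot accept, on 7 of 15 allowed days. This follows from the text and needs no assumption.

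The size does need assumptions. Each affected patient is worth 4 points of a 25-patient cohort's DCR. How many there will be is unknown; the 5 to 9 points (1.3 to 2.3 patients) rest wholly on the assumed SD rate, second-scan progression rate and scan-date spread, none of which the protocol gives. Reading DCR as CR+PR+SD is also an assumption, from ordinary usage, because the protocol does not spell it out.

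The consequence is modest: DCR is a secondary, descriptive endpoint with no decision rule, and the SD rule does not touch ORR, PFS or OS. It is worth correcting because the correction is simple.

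**What to change.** In Appendix 7, state the SD minimum as 6 weeks less the 7-day scan window: SD criteria met at least once, at least 35 days after first dose. Use the same limit in the best-response algorithm, for RECIST 1.1 and irRECIST. Express it as days elapsed since first dose, because 42 days elapsed is study Day 43 if Cycle 1 Day 1 is Day 1. If the SAP already sets a tolerance, bring the two documents into line.

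The cost is one sentence and one line of the algorithm, with no new data. There are two drawbacks. DCR can only rise, so the 35-day limit should be stated whenever DCR is compared with other trials. And the protocol is at amendment (e) of an open-label study, so loosening an efficacy definition now may look data-driven. To meet that, fix the rule before the analysis, record the reason as alignment with the scan window, and report DCR under the strict 42-day rule as a sensitivity analysis.
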